**Figure 2 F2:**
[figure not shown]
A The software “FOR KOA”: Login interface. B The software “FOR KOA”: Instruction video for cycle ergometer.

**Figure 3 F3:**
[figure not shown]
The bracelet for patients.

##### Osteoarthritis education

2.3.1.1

The purpose of osteoarthritis education is to let participants know their own situation, build up their confidence and encourage them to participate in treatment. Participants can communicate with physicians and physiotherapists through the application during this process. Physicians and physiotherapists can also push the content of knee OA on the application platform, including the introduction of popular science of knee OA, the latest research progress of knee OA rehabilitation, etc. Relevant contents will be published on the application platform every 2 weeks.

##### Self-management

2.3.1.2

Self-management will guide participants in three aspects: emotion management, weight management and medication management. Emotional management will be guided by psychotherapists through voice and video via the application platform. The participants will upload the body mass index on the application every week, and read the weight management and diet nutrition information pushed by the application platform. Medication management will be conducted under the guidance of physicians. If participants take other drugs during the trial, they will also actively record them on the application platform.

##### Land-based exercise programs

2.3.1.3

Land-based exercise programs include land aerobics (power cycling and walking) and strength training. Three times a week, 30 to 45 minutes each time, the exercise intensity was moderate (the range of metabolit equivalent is 3–6). The intensity of exercise is measured by the rating of perceived exertion (RPE). When the RPE reaches 12–14 or the heart rate reaches 70% of the maximum heart rate (maximum heart rate = 207-age ∗ 0.7), the moderate intensity of exercise is achieved.^[44]^ Participants will first assess under the remote guidance of physicians and physiotherapists in practice; then, physiotherapists will transmit exercise prescriptions and action teaching videos to participants through the application platform according to the assessment results; after physicians and physiotherapists confirming that they can correctly conduct action training through the feedback of participants’ image data, participants start to exercise program according to the exercise prescription. When the RPE of participants continues to decrease or the heart rate intensity fails to meet the requirements, the physiotherapist will make new exercise programs for them. The implementation place of exercise programs is in the community activity center and home. Power bikes will be placed in the activity center of community for every participant to do exercise.

The bracelet as wearable devices will be used to detect data of individuals in the process of exercise, monitor the movement of participants, and ensure the effective exercise of participants. The date of individuals in the process of movement will be uploaded every ten seconds, and all data will be saved in the database for storage. Physicians and physiotherapists who are responsible for guiding participants can log in from the computer and view the patient's movement data, which adjust the exercise prescription in real time. Furthermore, patients can leave messages to physicians and physiotherapists through the software platform instead of coming to the hospital in person for face-to-face communication. Physicians and therapists can also release relevant information of osteoarthritis education to patients through the software platform, and provide remote guidance to patients in all aspects.

#### Control group

2.3.2

Oral guidance including arthritis education, self-management and land-based exercise will be delivered from physicians and physiotherapists after the first assessment to the participants. Based on the specific situation of participants, the appropriate adjustments of the oral guidance will be made and recorded in a datasheet for analysis. In addition, the participants will be allowed to receive further intervention once the symptoms worsen. During the trial, the celecoxib and glucosamine hydrochloride are also required.

### Randomization and blinding

2.4

Participants will be randomly divided into the internet-based rehabilitation group and control group as the proportion of 1:1 according to the principle of random distribution after completing the baseline assessment for participants. The random numbers will be generated via computer software programs designed by statisticians who is blinded to the study content. The random number assigned to each group will be written on a piece of paper and placed in a sealed and opaque envelope. The envelope will be provided to the participants based on the randomization order. The assessors in the trial will not be aware of the random assignment for the participants. All the physicians and physiotherapists participating in the outcomes assessment and intervention guidance will receive a standardized training prior to this study, and will be allocated into these different two procedures during the trial. Physicians and physiotherapists involved in the assessment will not participate in the later experimental intervention. Data will be analyzed with blinding to group allocation in the data statistics.

### Withdraw

2.5

The participants in both groups can withdraw from the trial during the study. The researchers will notify the withdraw ones of potential adverse events and related managements, and record the withdrawal information, such as the reason, time and contact person.

### Outcome assessments

2.6

Outcomes assessments will be conducted at baseline, 6 weeks and 12 weeks post-intervention. All participants will be assessed by researchers who are blinded to the group assignment.

#### Primary outcome measures

2.6.1

It is foremost to explore the feasibility of internet-based rehabilitation program for the patients with knee OA in the community setting. To assess feasibility, data completeness will be examined as the proportion of participants in the internet-based rehabilitation group who meet the inclusion criteria but are unwilling to participate in the trial, as well as the satisfaction at the end of trial. The compliance of the participants from internet-based rehabilitation group will also be used as a reference index for feasibility. Each time the participants exercise in the community setting they can sign in after starting the program as long as they wear wearable devices. We consider it as high compliance when the number of participants completing the exercise accounts for 90% or more of the required number of times.

The contents of the survey are the overall satisfaction of the participants with the use of the application platform, as well as the satisfaction with osteoarthritis education, self-management and land-based exercise program, as well as the satisfaction with wearable devices in the research process. The results of satisfaction survey were conducted by using 5-point Likert scale. Participants will choose one answer from “very satisfied”, “satisfied”, “general”, “dissatisfied” and “very dissatisfied” under each question. The answers above correspond to 5, 4, 3, 2, and 1 points respectively.^[45]^ The final total score is calculated. The higher the final score of the questionnaire, the higher the satisfaction of the participants.

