**Methods::**

An assessor-blinded randomized controlled feasibility trial will be performed to study the feasibility and effectiveness of internet-based rehabilitation program for the patients with knee OA in the community setting. Forty participants with knee OA will be recruited and randomly allocated into internet-based rehabilitation group (IRG) or control group (CG). The interventions of IRG will be performed in the community setting via web-based platform and wearable devices. The outcome measures will be conducted at baseline, and post-intervention 6 weeks, 12 weeks during the study. The feasibility will be tested by the proportion of participants who will complete the internet-based rehabilitation program within 12 weeks in IRG as well as the compliance and satisfaction. Additionally, the effectiveness of internet-based rehabilitation will be assessed by the Western Ontario and McMaster Universities Osteoarthritis Index, 11-point Numerical Rating Scale and Short Form-36 quality-of-life questionnaire.

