#### Internet-based rehabilitation group

2.3.1

The purposely designed software “FOR KOA” enable the conduct of the internet-based rehabilitation programs, which mainly include arthritis education, self-management and land-based exercise programs according to the latest guidelines by Osteoarthritis Research Society International (OARSI).^[5]^ The bracelet matched with the software “FOR KOA” will automatically collect the heart rate, blood pressure and blood oxygen saturation of the participants during the exercise and display them, so as to allow the physical therapist to remotely monitor whether the participants’ exercise intensity meets the requirements (The software “FOR KOA”: A and B of Fig. 2; The bracelet for patients: Fig. 3). Participants will also be required to assess the outcome from the software “FOR KOA” at the beginning of the trial, after 6 weeks and 12 weeks. Participants may terminate the trial at any time and receive relevant treatment in case of symptom deterioration or other unexpected circumstances during the trial. During the trial, the celecoxib and glucosamine hydrochloride are also required.

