### Sample size

2.8

According to the previous statistical study, the recommended sample size of the feasibility trial is at least 12 in each group.^[50]^ 20 participants are recruited in each group and a total of 40 participants are recruited allowing for not less than 20% dropout rate of the period. The participants will help us to evaluate the mean and variability of the test results in order to provide plate beads for future larger scale research.

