### Statistical analysis

2.9

To evaluate the feasibility of the study, we will calculate the proportion of enrolled participants out of all eligible patients, participants who dropout rates. Besides, a patient satisfaction survey for the use of the “FOR KOA” will be collected and analyzed. For the feasibility index, the method of statistical description is contingency table, composition ratio and statistical chart.

Means and standard deviations will be used to describe between-group statistics of 11-NRS, WOMAC and SF-36. The measurement data will be assessed for normal distribution using Shapiro-Wilk test for both groups. For the data description of quantitative index, using 

 if it obeys normal distribution; if it does not obey normal distribution, use M ± (QU-QL). In statistical inference, repeated measurement analysis of variance (subject to normal distribution, homogeneity of variance and spherical symmetry), post-hoc test and rank sum test (not subject to homogeneity of normal distribution and variance) are used. Statistical analysis will be processed by SPSS software (version 24.0). The categorical variables will be compared by a chi-square test. *P* < 0.05 will be accepted as the threshold for statistical significance.

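### Satisfaction, a primary feasibility measure, is surveyed at the end of the trial with no survey named at withdrawal, so the score would mainly describe internet-group participants who stayed

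*Protocol article*

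**What the plan says.** The abstract puts satisfaction among the feasibility tests, after programme completion and together with compliance: "The feasibility will be tested by the proportion of participants who will complete the internet-based rehabilitation program within 12 weeks in IRG". Section 2.6.1 (Primary outcome measures) repeats satisfaction as a feasibility measure and gives its timing: "as well as the satisfaction at the end of trial". The questionnaire concerns the app, the education, the self-management, the exercise programme and the bracelet, so it applies to the internet group: "The contents of the survey are the overall satisfaction of the participants with the use of the application platform". Each question is answered on a five-point scale scored 1 to 5.

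For people who leave, section 2.5 (Withdraw) says the researchers will "record the withdrawal information, such as the reason, time and contact person". Satisfaction is not in that list. Section 2.3.1 tells the internet group: "Participants may terminate the trial at any time and receive relevant treatment in case of symptom deterioration".

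Section 2.8 recruits 20 per group, "allowing for not less than 20% dropout rate of the period". Section 2.9 reports dropout rates among the feasibility results and says that "a patient satisfaction survey for the use of the “FOR KOA” will be collected and analyzed". It gives no rule for participants who left.

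**The concern.** The questionnaire rates the parts of the programme that a participant might leave over: the app, the exercise, the device. A poor experience of any of them is a plausible reason to withdraw, so the missing ratings are unlikely to be a random subset. If the only survey falls at the end, the people whose opinion would be most informative about acceptability may be the ones without a score.

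At stake is how far the satisfaction figure can be trusted when a larger trial is planned. Taken alone, a survey of stayers can look better as more dissatisfied people leave. This is also a question of data collection rather than analysis: a rating that was not requested at withdrawal cannot be recovered later by an analysis plan.

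**Working it through.** **Timing, from the text**

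- Section 2.6.1 fixes satisfaction specifically at the end of the trial.
- Section 2.6 gives a general schedule of baseline, 6 weeks and 12 weeks for outcomes. The specific statement in 2.6.1 governs satisfaction. Even if a 6-week survey were read into the plan, anyone leaving before week 6 would still have no rating.
- Sections 2.5 and 2.9 name no survey at withdrawal.

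**How many ratings could be missing**

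Inputs from section 2.8: at least 12 per group recommended, 20 per group recruited, dropout of not less than 20%. Inflating 12 for 20% dropout gives 12/(1 − 0.20) = 15, not 20. Since 12/(1 − 0.40) = 20, the planned size keeps 12 per group at up to 40% dropout. The article states its inputs as lower bounds, so 20 is consistent with them and this is no error. It does give a sensible range of 20% to 40%. Assuming the same rate in the internet group:

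- 20% dropout: 0.20 × 20 = 4 without a rating, 16 with one.
- 40% dropout: 0.40 × 20 = 8 without a rating, 12 with one.

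**What that could do to the score**

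The document gives no satisfaction values, so those below are assumptions chosen to show the range.

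Mean per item over all 20 = (stayers × their mean + leavers × their mean)/20. With stayers at an assumed 4.5 and the leavers' unseen mean bounded by the scale at 1 and 5:

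| Dropout | Leavers' mean 1 | Leavers' mean 2 | Leavers' mean 5 |
|---|---|---|---|
| 20% | (16 × 4.5 + 4 × 1)/20 = 3.8 | (72 + 8)/20 = 4.0 | (72 + 20)/20 = 4.6 |
| 40% | (12 × 4.5 + 8 × 1)/20 = 3.1 | (54 + 16)/20 = 3.5 | (54 + 40)/20 = 4.7 |

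The overstatement is the dropout fraction times the gap between stayers and leavers. For example, 0.20 × (4.5 − 2) = 0.5 points per item.

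The share satisfied behaves the same way. If 14 of 16 stayers are satisfied (87.5%, assumed), the share among all 20 lies between 14/20 = 70% and (14 + 4)/20 = 90%.

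Both ranges include values above the observed figure, so an overstatement is possible and plausible but not forced.

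**The case against.** **Withdrawers are not expressly excluded.** No sentence bars them from the survey, and the list in section 2.5 is open, being introduced by *such as*. A full protocol may say more than the article. This stands: a reader might infer that leavers are never asked, and the text does not go that far. What it does support is that the only stated timing is the end of the trial and no exit survey is named.

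**Satisfaction does not stand alone.** Completion, compliance and dropout rates are also feasibility measures, and a programme that loses dissatisfied people would score worse on those. Withdrawal reasons are recorded, and with about four leavers they can be read one by one. No satisfaction threshold or progression rule is stated, so no stated decision turns on this score. All of this stands and lowers the stakes. It does not replace the ratings: a count and a reason are not answers on the app, education, self-management, exercise and device.

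**Leaving need not mean dissatisfaction.** Worsening symptoms or unexpected circumstances say nothing certain about the app or bracelet. This stands, and is why the direction of bias is likely rather than proven.

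**The total score.** Because section 2.6.1 says "The final total score is calculated", a reader might also infer that a badly rated component would be hidden in the sum. The document does not support that. Answers are collected question by question, section 2.9 plans contingency tables and composition ratios for the feasibility indices, and nothing says item results will be discarded.

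**Conclusion.** The point holds in a limited form. As written, satisfaction is measured at the end of the trial, and 4 or more of the 20 internet-group participants could have no rating at the dropout the plan allows for (8 at 40%). The score would then mainly describe those who stayed and is likely, though not certainly, too favourable.

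This rests on two assumptions: that dropout in the internet group is at least the overall 20%, and that leavers tend to be less satisfied than stayers. The size of any bias cannot be derived from the document. A stronger claim, that the measure is certainly inflated or misleads on feasibility as a whole, is not supported, because attrition is reported separately and no decision rule depends on satisfaction. This is a worthwhile, inexpensive improvement rather than a defect that undermines the trial.

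**What to change.** - In sections 2.5 and 2.6.1, state that internet-group participants are offered the same satisfaction questionnaire at withdrawal as well as at week 12.
- In section 2.9, report satisfaction with the number responding out of all randomised to the internet group, placed beside the dropout rate.
- If non-responders are counted as not satisfied, present that at most as a worst-case sensitivity figure. As a main result it would fold attrition, already a separate index, into satisfaction and would label people who left for unrelated reasons as dissatisfied.

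The cost is one added trigger for an existing short form and a few lines of wording. Internet-group questionnaire data are already held electronically (section 2.10), and withdrawal information is already collected. The downside is some refusals at withdrawal and possibly a less favourable figure.

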#### Secondary outcome measures

2.6.2

Pain of knee (s) will be assessed with a 11-point Numerical Rating Scale, 0 is no pain and 10 is worst possible pain.

The Western Ontario and McMaster Universities Osteoarthritis Index (WOMAC) will be used to measure pain, stiffness and physical function in the knee. WOMAC, a self-administered health-status instrument for patients with knee OA, consists of 24 items within three subscales: pain (five items), stiffness (two items) and physical function (17 items).^[46,47]^ All items are rated on a Likert scale of 0 (no symptoms)–4 (extreme symptoms), with a total range of 0–96 and higher scores indicating worse symptoms.

Quality of life will be assessed by means of the Short Form-36 quality-of-life questionnaire (SF-36). Zero points corresponds to the worst quality of life and 100 points corresponds to the best quality of life as put forward through the questionnaire.^[48]^

Adverse events will be recorded throughout the trial. The intensity and possible relationship with the treatment will be examined and described in detail if those once occurred.

Baseline assessment will be carried out after eligibility and informed consent have been confirmed. Demographic data referring to participant's age (in years), gender, height, weight, body mass index (BMI), physical functional data referring to physical activity (evaluated by the International Physical Activity Questionnaire (IPAQ) short version),^[49]^ education, occupation, source of income, hobbies and interests, marital, smoking and drinking status, medical history will all be collected.

### Safety measurement

2.7

Adverse events of participants will be monitored during the intervention. Any adverse events, including exercise injuries, will be reported in detail by the study assistant of the study group using the adverse event case report form (CRF).

### Sample size

2.8

According to the previous statistical study, the recommended sample size of the feasibility trial is at least 12 in each group.^[50]^ 20 participants are recruited in each group and a total of 40 participants are recruited allowing for not less than 20% dropout rate of the period. The participants will help us to evaluate the mean and variability of the test results in order to provide plate beads for future larger scale research.

### Statistical analysis

2.9

To evaluate the feasibility of the study, we will calculate the proportion of enrolled participants out of all eligible patients, participants who dropout rates. Besides, a patient satisfaction survey for the use of the “FOR KOA” will be collected and analyzed. For the feasibility index, the method of statistical description is contingency table, composition ratio and statistical chart.

Means and standard deviations will be used to describe between-group statistics of 11-NRS, WOMAC and SF-36. The measurement data will be assessed for normal distribution using Shapiro-Wilk test for both groups. For the data description of quantitative index, using 

 if it obeys normal distribution; if it does not obey normal distribution, use M ± (QU-QL). In statistical inference, repeated measurement analysis of variance (subject to normal distribution, homogeneity of variance and spherical symmetry), post-hoc test and rank sum test (not subject to homogeneity of normal distribution and variance) are used. Statistical analysis will be processed by SPSS software (version 24.0). The categorical variables will be compared by a chi-square test. *P* < 0.05 will be accepted as the threshold for statistical significance.

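### Assumption tests choose, outcome by outcome, between a three-visit repeated-measures ANOVA and an unspecified rank-sum test, and non-normal scores get an invalid summary that conflicts with the stated mean and SD

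*Protocol article*

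**What the plan says.** Section 2.9 (Statistical analysis) begins without condition: "Means and standard deviations will be used to describe between-group statistics of 11-NRS, WOMAC and SF-36". It then adds a test of normality: "The measurement data will be assessed for normal distribution using Shapiro-Wilk test for both groups". Description now depends on the result: "if it does not obey normal distribution, use M ± (QU-QL"), which I read as the median plus or minus the upper quartile minus the lower quartile.

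Inference depends on assumptions too: "repeated measurement analysis of variance (subject to normal distribution, homogeneity of variance and spherical symmetry), post-hoc test and rank sum test". The rank-sum condition reads "rank sum test (not subject to homogeneity of normal distribution and variance) are used". The section does not name the ANOVA effect to be tested, or the visit or score to which the rank-sum test applies. The general significance threshold is 0.05.

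Outcomes are assessed at baseline, 6 weeks and 12 weeks (section 2.6). Pain, WOMAC and SF-36 are secondary (section 2.6.2); feasibility is primary and analysed descriptively. Section 2.8 gives the purpose of the numerical results: "The participants will help us to evaluate the mean and variability of the test results", for a later, larger study. On size it states "the recommended sample size of the feasibility trial is at least 12 in each group" and "a total of 40 participants are recruited allowing for not less than 20% dropout rate of the period".

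**The concern.** The two routes do not answer the same question. A repeated-measures ANOVA compares mean profiles over three visits. A two-sample rank-sum test takes one value per person, compares distributions and gives no mean difference. When the data pick the route separately for each outcome, one scale may be reported as a difference in means over time and another as a rank comparison at a visit chosen later. With about 20 people per arm, the choice will often reflect chance or the coarseness of the scale.

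The descriptive rule has its own fault. An interquartile range is a width, not a margin on each side of the median, and the rule applies it where data are likely to be asymmetric. The same paragraph also promises mean and SD regardless, so a reader cannot tell which will be reported. The SD is what a planner of the larger trial needs.

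The classical ANOVA also has two costs in a 40-person trial that allows for dropout. By default it uses only people with all three visits. Its group main effect averages in the baseline visit, where no effect can exist.

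**Working it through.** **Inputs from the article.** 20 per arm, 1:1; dropout allowance 20%; three visits; threshold 0.05; pain on an integer 0–10 scale. **Assumptions, since the article gives no figure.** Shapiro-Wilk at 0.05, two-sided tests, within-person correlation 0.5 or 0.7, effect 0.8 SD at both follow-ups, pain mean 4.5 to 5 with SD 2.

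**The plan's own figure.** 12/(1 − 0.20) = 15 per arm, not 20. Both stated inputs are lower bounds, and 20 × 0.8 = 16 ≥ 12, so 20 per arm satisfies them. There is no error here, and nothing below depends on it.

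**1. How often the tests switch the method.** The text says the test covers both groups but not whether it is run at every visit.
- Two tests (both arms, one visit), truly normal data: 1 − 0.95² = 9.75%.
- Six tests (two arms, three visits): 1 − 0.95⁶ = 26.5%. Simulation with correlated visits gives 26–27%.
- Integer pain score, 20 per arm, simulated by rounding and clipping normal values to 0–10: about 25–26% with two tests and 56–60% with six. The scale's discreteness drives this.

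Variance checks would add to these rates.

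**2. The summary for non-normal data.**
- Normal data: the interquartile range is 1.35 SD, and median ± that width covers 82%, not the middle 50%.
- Skewed example (gamma, shape 1.5, scale 2): QL 1.21, median 2.37, QU 4.11. Width = 4.11 − 1.21 = 2.90. Lower end = 2.37 − 2.90 = −0.53, which is impossible on a scale that starts at 0.

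**3. Who is analysed.** With complete cases only, 40 × 0.8 = 32 at 20% dropout. If a further 10% missed week 6 (a rate the article does not give), 40 × 0.8 × 0.9 ≈ 29.

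**4. Dilution of the group main effect.** With the effect absent at baseline and present at both follow-ups, the average is (0 + 1 + 1)/3 = 2/3 of it: 0.8 × 2/3 = 0.53 SD. The group-by-time term is not diluted in this way, because it uses baseline as the reference.

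**5. Illustrative power.** Simulated with equal correlation between visits, 20 per arm, 20% lost by week 12 and week 6 complete. The adjusted analysis is a week-12 comparison with baseline as covariate.

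| Analysis | Correlation 0.5 | Correlation 0.7 |
|---|---|---|
| ANOVA, group main effect | 43% | 37% |
| ANOVA, group-by-time | 61% | 83% |
| Rank-sum at week 12 | 56% | 56% |
| Baseline-adjusted, week 12 | 70% | 85% |

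Figures are good to about 2 points. Type I error was about 5% for every method, so the differences reflect precision and not leniency.

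**The case against.** The strongest reply is that this is a feasibility trial. Its primary outcomes are descriptive, it has no power calculation, and the affected scales are secondary. Every candidate test holds its error rate. A condensed article may also leave the analysis set, missing-data rule and tested effect to a fuller document. All of that stands, and it limits the weight of the point. It does not remove what section 2.9 itself states: the data-driven choice of method and the faulty summary.

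Three stronger readings are tempting, and the article does not support them.
- **That the analysis ignores baseline.** It does not for the ANOVA: baseline is one of the three assessments, and the group-by-time term uses it. Only a rank-sum test on follow-up scores would ignore it, and the article does not say that follow-up scores rather than changes would be ranked.
- **That incomplete participants will be excluded.** This is the default behaviour of classical repeated-measures ANOVA, not a rule the article states. The 20% is also an allowance, not a forecast.
- **That the SD will be lost for non-normal outcomes.** The opening sentence of the paragraph promises mean and SD without condition. What is established is a contradiction.

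The power gain also depends on the comparator. Against the group main effect it is large. Against the interaction it is about 9 points at correlation 0.5 and 2 at 0.7. Adding an assumed 10% missed at week 6 would widen it, but the article offers no basis for that rate.

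**Conclusion.** The point holds in a limited form and should be corrected. Section 2.9 lets the data choose between two analyses with different targets, and one of these has no named visit or score. A truly normal outcome would be diverted in about 10% to 27% of trials, depending on how many Shapiro-Wilk tests are run at an assumed 0.05, and an integer pain score in about 25% to 60% under the assumed mean and SD. Median ± interquartile width is not a valid summary, and its use conflicts with the paragraph's first sentence and with section 2.8. These conclusions rest on the text.

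The loss of incomplete cases (about 32 of 40 kept) and the dilution to two thirds are properties of the classical method: the first by default, the second only if the group main effect is what is tested. The power figures are illustrative and rest on the assumed effect, correlation and dropout pattern. The consequence is confined to secondary outcomes and to the usefulness of the estimates for a later trial.

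**What to change.** - Delete the switch based on assumption tests.
- For each secondary score, prespecify one linear mixed model of the week-6 and week-12 values with arm, visit, arm-by-visit and baseline score, including every randomised participant with any follow-up. A community covariate is optional.
- Report the 12-week arm difference with its 95% confidence interval, and give a bootstrap interval as a check where scores are skewed.
- Always report mean and SD by arm and visit. Where scores are skewed, add median (QL, QU) in place of the ± form. This also removes the contradiction within section 2.9 and serves the aim in section 2.8.

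The cost is a short change to the analysis wording. The variables are already collected at the planned visits, and the model can be fitted in the named SPSS version.
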